***9.2.*** ***Handling of blood samples***

*9.2.1.*        *Extractions*

After administration of palonosetron, there will be blood samples (5 ml) at the following times: end of infusion, 10 - 15 - 30 - 45 - 60 mins, 1,5 - 2 - 3 - 4 -8 to 12 hours. If income permits 24 hours.

Blood will be drawn from the vein. EDTA tubes are used (5 ml).

Samples were centrifuged at 3500 rpm for 10 minutes at 4 ° C within 30 minutes after removal. The resulting plasma was separated into two aliquots for determination of palonosetron, and freeze at -70 ° C until shipment to the laboratory for analysis. Palonosetron determining aliquots of plasma will be by high resolution liquid chromatography with mass spectrometer detection (LC / MS). The conditions of sample handling can be modified depending on the analysis technique, which is in development.

*9.2.2.*        *Labelling*

Samples for the determination of palonosetron is labeled with the following information:

-           Line 1:               Name of the active ingredient (palonosetron).

-           Line 2:               study identification code. Route of administration. Aliquot (original or duplicate).

-           Line 3:               Number of subject randomization. Initials. Period administration.

-           Line 4:               The time of extraction.

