**11. - Design.**

Open, crossover, controlled trial in two phases. There shall be a minimum washout period of 14 days.

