***6.2.*** ***Randomization***

Subjects will be randomly assigned to each of the two treatment sequences.

The randomization number will be the one used to identify patients included in the study and will be reflected in the documents of the study.

Randomization was performed when deciding the administration of the first dose of medication. It will randomize the order of the route of administration under consideration by the list in Annex IX.

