***8.2.*** ***Dosing Schedule***

This is a single dose study. Patients will receive on two separate occasions a single palonosetron dose of 250 μ g, once the administration is subcutaneous, intravenous in the other. The order of the route of administration will be allocated according to a randomization table.

*8.2.1.*        *Procedures medication administration*

The administration of medication will be as follows:

- First cycle: sc or iv administration, 30-60 minutes before chemotherapy administration.

- Second cycle: sc or iv infusion (the opposite way than first cycle), 30 - 60 minutes before the administration of chemotherapy

The order of the route of administration depends on the randomization table. The administration will be in the abdomen when subcutaneously. In the case of intravenous administration, the same route may be used in place for administration of chemotherapy or other medications that the patient should receive as their medical criteria.

Intravenous administration will be performed quickly, in 30 seconds, as described in the Product data sheet.

Subcutaneous administration will also perform at this time, in the abdomen.

*8.2.2.*        *Washout*

Has established a washout period between the two administrations of 14 days, which is considered sufficient as the pharmacokinetic data observed palonosetron in the literature.

*8.2.3.*        *Precautions, antidotes*

Available emergency equipment and standard operating procedure for the treatment of non-specific reactions (allergy, anaphylactic shock). At all times there will be a doctor reachable to respond to unforeseen developments.

*8.2.4.*        *Procedures blind*

It is an open, not hidden treatments either the researchers nor the volunteers, but for those responsible for drug quantification analysis.

*8.2.5.*        *Concomitant medication*

The investigator assessed the impact on the study in the event that any of the volunteers had to receive some treatment concomitantly.

Will try the two periods of administration of study medication are similar in concomitant medication.

*8.2.6.*        *Adherence*

Adherence will be secured by the research team, who directly administer the medication. Log the exact times of drug administration and removal of samples.

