Each extraction with 5 ml of blood obtained. Samples were extracted in 5ml tubes through an Abbocath ® or a similar device placed in the arm contralateral to the administration of chemotherapy.

The track maintenance extraction will take place in optimum conditions by introducing, after each drawing 5 ml of a solution prepared with 1 ml of 1% sodium heparin, and 9 ml of 0.9% NaCl through the device.

Drawing the samples will be transferred into a glass with ice to the Laboratory of Clinical Pharmacokinetics Clinical Research Unit, where they are processed and frozen until analysis. The manipulation of the samples, the biological matrix and the storage temperature will be confirmed by the technician in charge of the analysis.

The determination of plasma concentrations of palonosetron be performed by HPLC.

*9.1.3.*        *Stage final review*

At least two weeks after the last drug administration, before the next cycle, check the patient's situation, using the same criteria as the selection period.

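### The sample labels print the route of administration, so the assay staff see the treatment that section 8.2.4 says is hidden from them

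*Protocol*

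**What the plan says.** The summary calls the trial "Open, crossover, controlled trial in two phases". Section 8.2.4, on blinding procedures, says who knows the treatment: "It is an open, not hidden treatments either the researchers nor the volunteers", followed directly by the exception "but for those responsible for drug quantification analysis". In plain terms, investigators and patients know the route and the people who quantify the drug do not.

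Section 9.2.2 introduces the label with "Samples for the determination of palonosetron is labeled with the following information". Line 1 names the active ingredient. Line 2 is "study identification code. Route of administration. Aliquot (original or duplicate". Line 3 is "Number of subject randomization. Initials. Period administration". Line 4 is the extraction time. The rule has no exception, and no separate masked label is described.

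On the sequence of routes, section 6.2 says: "It will randomize the order of the route of administration under consideration by the list in Annex IX". Section 9.1.2 sends the samples to the "Laboratory of Clinical Pharmacokinetics Clinical Research Unit, where they are processed and frozen until analysis". Section 10.1 places the quantification in that same unit, and section 12.1 gives the unit the pharmacokinetic and statistical analysis as well.

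**The concern.** An analyst who handles a tube labelled under section 9.2.2 reads on it the fact that section 8.2.4 says is concealed. This is the only masking in an otherwise open study.

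The assay is the source of every primary result. Section 10.1 takes Cmax and tmax directly from the observed concentrations and AUC0-t from the same concentrations by the trapezoidal method. Section 12.1 then forms bioavailability as the ratio of the subcutaneous to the intravenous AUC0-t. Because Cmax and tmax are single observed points, one value accepted, repeated or rejected could move them. If such decisions involve judgement, an analyst who knows the route also knows which profile to expect. Section 9.2.1 adds that the analytical technique is still being developed, so the protocol itself sets no handling rules that would limit discretion.

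**Working it through.** The protocol gives no figure to reproduce. The check compares the sections and then counts the samples covered.

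**Step 1. Is the route the same thing as the treatment?** Sections 8.1 and 8.2 give the same product and the same 250 μg dose in both periods, and only the route differs. Knowing the route is therefore knowing the treatment.

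**Step 2. Do the two rules collide?**

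| Section | Rule | Consequence for the analyst |
|---|---|---|
| 8.2.4 | Treatment is open to investigators and patients, but not to those who quantify the drug | Should not know the route |
| 9.2.2 | Palonosetron samples carry the route on line 2, for original and duplicate alike | Reads the route on the tube |

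**Step 3. Is there a step that reconciles them?** A recoding, over-labelling or masking step before assay would do so. None appears in the handling instructions (9.1.2, 9.2.1), the labelling rule (9.2.2), the pharmacokinetic evaluation (10.1) or elsewhere in the protocol.

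**Step 4. How many samples are covered?** Inputs: a baseline draw (9.1.2); post-dose draws at end of infusion, 10, 15, 30, 45 and 60 minutes, and 1.5, 2, 3, 4, 8 and 12 hours, with a 24-hour draw only if the hospital stay allows (9.1.2, 9.2.1); two periods; 25 evaluable patients (7.1, 7.6); two plasma aliquots per sample (9.2.1).

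- Draws per period: 1 + 12 = 13, or 14 with the 24-hour draw.
- Blood samples: 13 × 2 × 25 = 650, or 14 × 2 × 25 = 700.
- Labelled plasma aliquots: 650 × 2 = 1,300, or 700 × 2 = 1,400.

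The count treats 8 and 12 hours as two draws, assumes the baseline sample is split like the others, and leaves out samples from patients who are later replaced.

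**Step 5. Is the route needed to identify a sample?** No. Randomization number, period, extraction time and aliquot identify each one within the study. Number and period can be linked to the route afterwards through Annex IX. The same link means that deleting the route from the label masks the analyst only if the analyst does not hold that list.

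**The case against.** The strongest reply is that little harm follows:

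- Section 9.2.1 specifies liquid chromatography with mass spectrometry, an instrumental readout, and section 10.1 says the centre is GLP-certified.
- The protocol does not provide for discretionary re-integration, re-assay or rejection of values.
- The objective is exploratory, section 6.1 calls the study a pilot, and section 12.1 describes the subcutaneous parameters without a confirmatory test or margin.
- If intravenous concentrations peak at once and subcutaneous ones later, the end-of-infusion, 10-minute and 15-minute values may reveal the route whatever the label says.

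All of this stands, and it limits the likely effect. It does not make the two sections compatible. Inferring the route from finished results is also weaker disclosure than reading it on each tube before the run.

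A second reply is that the masking rests on one awkward clause in a translated text. That is fair as a caution. However, in a section on blinding, singling out the assay staff makes sense only as an exception to the openness.

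A reader might go further and infer that the primary results will be biased or cannot be relied on. The document does not support that. It shows that a claimed safeguard is absent. The path from knowing the route to a distorted concentration is an assumption, and its size cannot be computed from the protocol.

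**Conclusion.** The point holds as an internal contradiction. Section 8.2.4 conceals treatment from the assay staff and section 9.2.2 discloses it on every label, about 1,300 to 1,400 plasma aliquots from 650 to 700 blood samples. Those counts show how far the labelling rule reaches and do not measure bias.

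The conclusion rests on reading section 8.2.4 as an exception to openness, and on the absence of any recoding step in the protocol. Bias through integration, repeats or rejection is possible but assumed, and probably small. The correction is still worth making: every primary parameter depends on this assay, and the protocol would otherwise claim a masking that does not exist. Nor should the correction be credited with complete masking, since early profiles may still suggest the route.

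**What to change.** In section 9.2.2, delete the route of administration from label line 2. Keep the study code, randomization number, period, extraction time and aliquot.

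Add to section 8.2.4 or 9.2 that the assay analysts do not receive the Annex IX list until the concentrations of each run are final. State that this includes the runs for the first four patients, whose pharmacokinetics are analysed before further inclusion (section 6.4).

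The cost is a changed label and a simple access restriction. The restriction needs someone to apply it, because one Clinical Research Unit does both the assay and the analysis. Nothing changes for patients, sampling or treatment.

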***9.3.*** ***Duration of study***

The clinical trial will consist of a selection phase, the intervention phase (or treatment) and final review visit.

In the selection phase, each subject will be selected for participation in the study during the 20 days prior to drug administration. Intervention phase include two treatment periods with a minimum of washing including 14 days, calculated taking into consideration the mean elimination half-life of palonosetron described in the literature (t1 / 2 = 40 hours). Each patient will receive the medication twice. They collected blood and urine samples as specified. The final review is held after the second treatment cycle.

**10.** **RESPONSE EVALUATION**

***10.1.*** ***Pharmacokinetic evaluation***

The quantification will be palonosetron concentrations in the Laboratory of Pharmacokinetics. Clinical Research Unit. University Clinic of Navarra. The Center is certified in Good Laboratory Practices.

With plasma concentration data at different times are calculated palonosetron pharmacokinetic parameters.

Primary parameters are considered in this study:

Cmax = maximum concentration. Its value will be extracted from the experimental data.

AUC _0-t_ = Area under the plasma concentration curve from time 0 to the last quantifiable concentration (time t) calculated by the trapezoidal method.

tmax =               time to reach Cmax. Its value will be extracted from the experimental data.

Security variables are:

VAS at different measurement times (baseline, and after the administration at 1, 4 and 8 hours)

Exploration of the administration at the same times.

The safety variables also include the description of the adverse events reported by patients or alterations in tests.

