***5.2.*** ***Secondary objective***

To assess the local tolerance of palonosetron (VAS pain, skin changes).

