***6.4.*** ***Design Justification***

The pharmacokinetic characteristics determine the estimated times of sampling, trying to define the likely tmax with subcutaneous administration and cover the entire absorption range.

The washout period is also conditioned by the terminal elimination half-life of palonosetron.

Since it is intended to assess bioequivalence, if not check if absorption occurs and what is the maximum concentration value is not considered appropriate to prolong the patient admission or request the removal of blood samples beyond the set range, which matches the patient's income for conrrespondiente chemotherapy.

Since there are no data on the absorption of subcutaneously palonosetron, pharmacokinetic analysis will be performed for the first four patients complete before continuing to include more patients. Special attention also to the local tolerance, but since it is a drug that is usually administered intravenously, with no evidence of phlebitis particular risk, it is considered that it should not have problems in this sense. Administration has been decided in the abdomen because it is necessary to administer a volume of 5 ml, since each vial contains the total dose diluted in this volume.

Using a dose of 250 μ g, which is the recommended sheet, in a single administration 30 minutes before administration of chemotherapy. Therefore maintaining marketing holder recommendation. In subcutaneous administration are to apply the same criteria.

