**9.** **ASSAY DEVELOPMENT**

***9.1.*** ***Study Plan***

*9.1.1.*        *Selection stage*

In the 20 days before the start of the intervention phase of the study will be the selection of volunteers. This phase will recruit 25 patients will be informed of the design, objectives and possible risks of the study. Each patient will have the opportunity to ask any questions you want to research. Before any test is obtained written informed consent.

They perform a complete medical history that includes:

• Detailed anamnesis.

• Complete physical examination with assessment of functional status (ECOG scale).

• Registration of drugs administered to the patient at the time of inclusion.

• Laboratory tests:

Hematology: CBC.

Biochemistry: blood: cre atinina, urea, SGOT (AST), SGPT (ALT), GGT, total bilirubin, electrolytes

In case the patient has already been subjected to this analysis in the 10 days prior to administration of the medication can not be repeated.

With all these data verify the eligibility of patients to participate in the study.

*9.1.2.*        *Intervention phase*

The intervention phase will consist of two periods in which the patient will receive the study medication. Each will have a minimum duration of 12 hours, separated by at least two weeks washout period. In each volunteer will receive a dose of palonosetron 250 μ g intravenously or subcutaneously, according to the randomization code. Before the second administration of the drug is verify that the patient has adequate hepatic and renal function.

Will place a peripheral venous independent pathway by the patient receive chemotherapy and palonosetron, through which the blood samples drawn for determination of the drug.

They undertake every single day of intervention:

- Determination of the SBP and DBP, FC and temperature in a sitting position before administration of the study medication.

Blood drawn at baseline (5 ml).

Assessment of pain by visual analog scale.

After drug administration was performed:

Blood samples (5 ml) at the following times: end of infusion, 10 - 15 - 30 - 45 - 60 mins, 1,5 - 2 - 3 - 4 -8 to 12 hours. If income permits 24 hours.

Collection of urine during the 12 hours of study.

Subjective assessment of pain using a visual analog scale at the time: 1 to 4 and 8 hours.

Physical examination of the administration at 1, 4 and 8 hours after administration.

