**11.** **Safety Assessment**

Patients remain in contact with the Center's staff, having received the medication under supervision and being evaluated in conjunction with each of the blood samples. A doctor will be available throughout the study at any time.

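### Local tolerance, the only secondary objective, has no pain score and no scheduled site examination between dosing and 1 h after a 5 ml abdominal injection

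*Protocol*

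**What the plan says.** Protocol section 5.2 gives one secondary objective: "To assess the local tolerance of palonosetron (VAS pain, skin changes". Section 6.4 explains the site of the subcutaneous dose: "Administration has been decided in the abdomen because it is necessary to administer a volume of 5 ml". Section 4.2 says that no local tolerance data exist for palonosetron and that patients will be watched closely in this respect. Section 6.4 also promises special attention to it.

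The measurement times are in two places. Section 10.1 lists the pain score as "VAS at different measurement times (baseline, and after the administration at 1, 4 and 8 hours" and puts the site examination at the same times. Section 9.1.2 has a pain score before dosing, then "Subjective assessment of pain using a visual analog scale at the time: 1 to 4 and 8 hours", and for the site "Physical examination of the administration at 1, 4 and 8 hours after administration".

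Blood is drawn much more often early on. Section 9.1.2 starts the post-dose series with "end of infusion, 10 - 15 - 30 - 45 - 60 mins". Section 11 describes patients as "being evaluated in conjunction with each of the blood samples", and section 11.1 has staff ask a general question about physical condition at each draw. Any event is recorded with its onset, course, duration and intensity. Section 8.2.1 places palonosetron 30 to 60 minutes before chemotherapy.

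**The concern.** Pain from a bolus injection, and any brief skin reaction to it, may well be greatest during the injection and soon after. The protocol's two instruments for local tolerance are both silent in that interval. The first post-dose score comes at 1 h, when chemotherapy is due to be starting or already running, so the one interval free of chemotherapy effects carries no score.

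At stake is what the trial can say on its secondary question. Post-dose VAS values close to baseline would be consistent with a painless injection, and equally with a painful one that had settled before anyone took a score. A later analysis plan cannot recover scores that were never taken, so the matter belongs in the protocol.

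**Working it through.** The protocol gives no figure to reproduce here. The check is a count from its schedules.

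**Inputs.** VAS times: sections 9.1.2 and 10.1. Site examination times: sections 9.1.2 and 10.1. Blood draws: sections 9.1.2 and 9.2.1. Adverse-event questioning: sections 11 and 11.1. Start of chemotherapy: section 8.2.1. Number of patients: section 7.1.

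| Contact after dosing | VAS | Scheduled site examination | Blood draw with general question |
|---|---|---|---|
| End of infusion | no | no | yes |
| 10 min | no | no | yes |
| 15 min | no | no | yes |
| 30 min | no | no | yes |
| 45 min | no | no | yes |
| 60 min | yes | yes | yes |

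**Step 1. Count before 1 h.** VAS scores: 0. Scheduled site examinations: 0. Blood-draw contacts: 5. The end of infusion is not defined for a subcutaneous injection; without that contact the count is 5 − 1 = 4.

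**Step 2. Do the two VAS schedules agree?** Section 9.1.2 could be read as a range from 1 to 4 hours, where section 10.1 lists 1, 4 and 8. On either reading the first post-dose score is at 1 h, so the count does not change.

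**Step 3. Position against chemotherapy.** Chemotherapy is due 30-60 min after palonosetron and the first score is at 60 min. The gap from the due start to the first score runs from 60 − 60 = 0 to 60 − 30 = 30 min. The first post-dose score therefore falls at or after the scheduled start in every case.

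**Step 4. What covers the first hour instead.** The question in section 11.1 asks about any difference in physical condition. It mentions neither pain nor the administration site. Section 11.1.1 grades intensity mainly by limitation of usual activities, a blunt scale for brief injection pain in a patient who is in hospital for 12 hours (section 4.2). It gives no VAS value, so the routes cannot be compared on VAS in this interval.

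**Step 5. Direction.** If early subcutaneous pain has faded by 1 h, the 1, 4 and 8 h scores understate it and the VAS results favour the subcutaneous route. If it persists to 1 h, the schedule records it, though possibly below its peak. The documents do not say which holds.

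**The case against.** The strongest reply is that early reactions are not unobserved. Staff are with the patient at every draw, they ask about changes, and they record complaints and their own observations with onset and intensity. The definition of a severe event mentions pain, and section 10.1 lists adverse events among the same safety variables as the VAS. A skin reaction that lasts to 1 h is seen at the 1 h examination. All of this stands. A reader might infer that early pain and skin reactions are missed altogether; the protocol does not support that. What remains is that they are captured only by a non-specific question on a three-level grade.

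A reader might also infer that peak pain would be recorded in none of the 25 subcutaneous administrations. That depends wholly on pain resolving before 1 h, for which the documents give no time course.

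Nor can it be established that the pain score is unrelated to the injection site. Section 5.2 names it as a measure of local tolerance, and the exact wording may be in the data collection notebook (Annex I, section 16.1), which is not shown. A baseline score in each period and the crossover also deal with stable background pain.

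Finally, this is a pilot study with no threshold or decision rule for local tolerance. A verdict favouring the subcutaneous route would be a reader's interpretation of the results; the plan does not fix one.

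**Conclusion.** The point holds as a gap in measurement. The protocol's own scale for its only secondary objective has 0 VAS scores and 0 scheduled site examinations between dosing and 1 h, while 5 blood-draw contacts (4 without the end of infusion) fall in that time. Early local reactions rest on general adverse-event questioning, and no VAS comparison of the routes is possible before chemotherapy is due to start.

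The count comes directly from the schedules and needs no assumption. The possible bias towards the subcutaneous route needs one, that early pain fades before 1 h, and its size cannot be given from the documents. The primary pharmacokinetic objective is untouched. This is a cheap improvement and not a flaw that endangers the trial.

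**What to change.** In sections 9.1.2 and 10.1, add a VAS worded as pain at the administration site, together with a site inspection, at the end of administration and at 15 and 30 min, in both periods. State what the end of administration means for the subcutaneous route. Keep the 1, 4 and 8 h assessments and report the early scores alongside them. The early scores need not replace the later ones as the summary of local tolerance.

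Cost: 3 extra VAS marks and 3 site checks per period, or 3 × 2 = 6 of each per patient and 6 × 25 = 150 of each over 25 completed patients. All fall at contacts already scheduled for blood draws, so no extra visit, blood sample or patient is needed. The data collection notebook needs matching fields.
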